#### Qualitative interview study

##### Recruitment

Eligible participants for Group 1 will be contacted via the email addresses and/or phone numbers provided while completing the baseline and 6-month follow-up questionnaires. Participants will be invited by email to share their experiences in a qualitative interview. If recruitment is insufficient using email alone, participants will be contacted by phone (either phone call or text message) to ascertain interest in the interview study. Recruitment will continue until approximately 12 individuals have been sampled in each category of the sampling frame.

Eligible participants for Group 2 will be purposively sampled via existing professional contacts known to the research team. Following initial outreach, snowball sampling will be used until 12 professionals, who were involved in the implementation of staff supports in the NHS, have been recruited.

##### Consent

Those expressing an interest in participation will be emailed a PIS and consent form, which they can return via email. Once consent has been obtained, participants will be contacted again to arrange a time suitable to them to be interviewed remotely (via MS Teams/Zoom, or telephone). Interviews are expected to last approximately 30–60 min, will be conducted at a time convenient for the participant and will be recorded with an encrypted Dictaphone. Recordings will later be destroyed following transcription, de-identification and pseudo-anonymisation of interview transcripts.

##### Data collection

Participants will initially be asked to briefly explain their role and to describe how it did/did not change since the onset of the COVID-19 pandemic. Participants will then be asked about the following: their perceived personal need of support within the NHS and what type of support is needed; their experiences with existing staff support programmes including why they did/did not use them; perceived barriers to access; perceived utility of staff support interventions during the pandemic and in general; other external forms of supports used; suggestions for how supports could be improved in their timing, targeting and content. Before the end of the interview, participants will be given the opportunity to add anything they feel is important that has not been discussed. Participants will receive a £25 Amazon voucher to thank them for their time.

### Study flow chart

Participants will enter the study and be offered the opportunity to participate in different components as outlined in figure 1.

**Figure 1 F1:**
[figure not shown]
Flow chart of study timings and components. CAPS-5, Clinician-administered PTSD Scale; CIS-R, Clinical InterviewSchedule-Revised; PTSD, post-traumatic stress disorder.

### Analysis plan

#### Longitudinal cohort study

Response weights will be calculated for each Trust, generated using a raking algorithm based on age, sex, ethnicity and role (using Trust population data obtained from Human Resources), with missing demographic data imputed using multiple imputation (for the purposes of weighting only). Trusts with response rates under 5% will be dropped from the analysis. Representativeness of the sample will be described using frequencies and percentages, and descriptive statistics given for each variable to summarise participants (frequencies and weighted percentages for categorical variables, mean and SD for continuous variables). We will examine differences between participants completing only the short survey, compared with those completing both the short and long surveys. We will summarise the weighted prevalence of the primary and secondary outcomes, stratified by sociodemographic and occupational factors. We will explore potential longitudinal associations between sociodemographic characteristics and occupational factors with the outcome measures (eg, GHQ-12, GAD-7, PHQ-9, AUDIT, PCL-6, MIES). Three-level random intercept linear or logistic (depending on the distribution of the outcome) regression models will be used to account for the hierarchical structure of the data, considering observations from baseline, 6-month follow-up and 12-month follow-up at level 2 and NHS trusts at level 3. We will use a measure of pressure on Trusts as the key exposure (eg, ratio of beds in use to staff numbers, ie, those not on sick leave), plotting levels of this exposure over time (aggregated at the Trust level), before partitioning the data into meaningful periods corresponding to burden level over the baseline data collection period (April 2020 to January 2021). We will plot all measures over time to look at patterns between this exposure and outcome levels, and use three-level random intercept logistic and linear regression models, as appropriate, to explore factors associated with outcomes in each period.

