### Measures

#### Longitudinal cohort study

##### Baseline

The baseline survey will involve a short survey (5–10 min) which collects information on the following topics: (1) Contact details, (2) Occupational information (eg, occupational group, length of professional registration), (3) Sociodemographic characteristics, (4) Working practices (eg, access to PPE, performing aerosolising procedures), (5) Perceived support from managers, colleagues, friends and family, (6) COVID-19-related questions (eg, suspected infection status, COVID-19 test status, isolation/quarantining), (8) Staff support programme access, (9) Self-reported diagnosed health conditions and (10) Common mental disorders. The prevalence of probable common mental disorders will be assessed using the 12-item GHQ-12, with a cut-off score of 4 or more indicating caseness.^13^

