There will be the option for participants to complete an additional longer survey (10–15 min), which includes information on the following: (1) Impact of COVID-19 (eg, on family, income, health, positive and negative changes in personal life or work), (2) Work experiences (leadership and teamwork, sickness absence, unsafe clinical practices, preparedness), (3) Usefulness of staff support programmes, (4) Caring responsibilities outside of work, (5) Confidence in institutions to handle the COVID-19 pandemic. In addition, the following validated measures will be used in the longer survey: the 7-item Generalised Anxiety Disorder (GAD-7) Scale to measure probable moderate anxiety disorder with a cut-off score of 10 or more indicating caseness;^17^ the 9-item Patient Health Questionnaire (PHQ-9) to measure probable moderate depression with a cut-off score of 10 or more indicating caseness;^18^ the 10-item Alcohol Use Disorder Identification Test to measure alcohol consumption with a cut-off score of 8 or more indicating hazardous drinking;^19^ the PCL-6 civilian version to measure PTSD with a cut-off score of 14 or more indicating the presence of probable PTSD;^15^ the 9-item Moral Injury Event Scale (MIES) to measure moral injury, with a higher score indicating greater exposure to morally injurious events;^20^ the 14-item Warwick-Edinburgh Mental Well-being Scale (WEMWBS) to measure subjective well-being and psychological functioning, with a higher score indicating a higher level of mental well-being;^21^ the 6-item Brief Resilience Scale (BRS) to measure psychological resilience, with a higher score indicating a higher level of resilience;^22^ the 12-item Burn-out Assessment Tool (BAT) to measure burn-out, with a cut-off score of 3.02 indicating probable burn-out.^23^ All validated measures use Likert Scale response options.

We will also assess suicidal ideation in the longer survey, using items related to suicidal thoughts, suicide attempts and self-harm derived from the CIS-R.^14^ We will measure fatigue using three novel items exploring: (1) Emotional and physical exhaustion on a 0–10 scale; (2) Whether any experienced fatigue is greater than usual tiredness (yes/no); and (3) Whether any experienced fatigue interferes with the ability to do things (yes/no).

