##### Follow-up—6 months

The 6-month survey will also involve a short version and long version. The short survey will collect information on the national and local staff support programmes used, and on household income. The same questions as at baseline will be asked regarding: COVID-19 experiences (eg, suspected infection status, COVID-19 test status, isolation/quarantining); teamwork; support from colleagues and friends/family. The same measures will be used in the 6-month survey as at baseline, as follows: GHQ-12, GAD-7, PHQ-9, Alcohol Use Disorders Identification Test (AUDIT), PCL-6, MIES and the CIS-R suicidality questions. In addition, the short form of the Post-traumatic Growth Inventory will be used.^24^

The long survey will collect the same measures as at baseline: WEMWBS, BRS, BAT, Fatigue. It will also collect information on the personal and occupational factors as at baseline. The topics covered may be updated as the pandemic evolves, in order to capture the most relevant information.

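### Five outcomes move from an optional long survey at baseline to the short survey at 6 months, and the stated weights cannot correct opt-in that depends on mental health

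*Protocol article*

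**What the plan says.** **Baseline** (Protocol article, Measures, Longitudinal cohort study). The short survey carries GHQ-12: "The prevalence of probable common mental disorders will be assessed using the 12-item GHQ-12, with a cut-off score of 4 or more indicating caseness". A second module is voluntary: "There will be the option for participants to complete an additional longer survey". The other scales sit there: "In addition, the following validated measures will be used in the longer survey". The list that follows includes GAD-7, PHQ-9, AUDIT, PCL-6 and MIES, and also WEMWBS, BRS and BAT.

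**6 months** (Follow-up—6 months). The paragraph on the short survey states: "The same measures will be used in the 6-month survey as at baseline, as follows: GHQ-12, GAD-7, PHQ-9", and continues with AUDIT, PCL-6 and MIES. The next paragraph leaves a smaller set in the long module: "The long survey will collect the same measures as at baseline: WEMWBS, BRS, BAT, Fatigue". The 12-month survey is to be similar.

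**Analysis** (Analysis plan, Longitudinal cohort study). On weighting: "Response weights will be calculated for each Trust, generated using a raking algorithm based on age, sex, ethnicity and role". Missing demographic data are "imputed using multiple imputation (for the purposes of weighting only". The plan will compare people who did only the short survey with those who did both, report weighted prevalence of the outcomes, and fit three-level random-intercept models over the three waves to outcomes that include all five scales.

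**The concern.** Prevalence of distress is a primary objective and its pattern over time a secondary one. For five of the named outcomes, the baseline figure comes from a self-selected part of the respondents. The 6-month figure comes from everyone who answers the short survey, including people never measured on these scales at baseline, because follow-up invitations go out whether or not earlier surveys were completed.

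The decision to spend another 10 to 15 minutes on a mental health survey may well depend on how the person feels. Raking to Human Resources totals on age, sex, ethnicity and role removes only the part of that dependence that those four variables carry. The study does hold a measure of distress for short-survey respondents, GHQ-12, but no stated weight or model uses it for this purpose. What is at stake is a biased baseline level and a shift in who was measured being read as a shift in mental health.

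**Working it through.** **1. Module placement, from the Measures section.**

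| Measure | Baseline | 6 months |
|---|---|---|
| GHQ-12 | short | short |
| GAD-7, PHQ-9, AUDIT, PCL-6, MIES | long (optional) | short |
| WEMWBS, BRS, BAT, fatigue | long (optional) | long |

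Only the middle row changes population because of the module. The suicidality items move in the same way as that row.

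**2. Bias in baseline prevalence.** The protocol gives no opt-in rate or expected prevalence for the cohort, so there is no figure to reproduce and every input here is an assumption. Let g be GHQ-12 caseness, r1 and r0 the long-survey opt-in among cases and non-cases, and p1 and p0 the PHQ-9 caseness in those groups.

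- True prevalence = g·p1 + (1−g)·p0
- Observed among opt-ins = [g·r1·p1 + (1−g)·r0·p0] / [g·r1 + (1−g)·r0]

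Take g = 50%, p1 = 50%, p0 = 8%. True prevalence = 0.5×0.50 + 0.5×0.08 = 29.0%.

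| Opt-in, cases / non-cases | Observed | Bias (points) |
|---|---|---|
| 60% / 60% | 29.0% | 0 |
| 65% / 55% | (0.1625 + 0.0220)/0.60 = 30.75% | +1.75 |
| 70% / 50% | (0.1750 + 0.0200)/0.60 = 32.5% | +3.5 |
| 55% / 65% | (0.1375 + 0.0260)/0.60 = 27.25% | −1.75 |
| 50% / 70% | (0.1250 + 0.0280)/0.60 = 25.5% | −3.5 |

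With g between 40% and 60%, the bias for these opt-in patterns stays within about 3.5 points either way. If true prevalence does not change and 6-month response is unselected, the same amount with opposite sign appears as change in a raw wave comparison.

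**3. What a longitudinal model does to it.** A simulation in SD units with no true change assumed these correlations: baseline GHQ with baseline PHQ 0.75, baseline PHQ with 6-month PHQ 0.60, baseline GHQ with 6-month PHQ 0.50. Opt-in depended on whether GHQ was above or below its mean.

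| False change (SD) | Opt-in 55% / 65% | Opt-in 50% / 70% |
|---|---|---|
| Difference of wave means | 0.049 | 0.099 |
| Likelihood estimate without GHQ-12 | 0.029 | 0.060 |
| Opt-ins measured at both waves, unweighted | 0.016 | 0.033 |
| Wave means, opt-ins weighted by GHQ-12 | 0.000 | 0.000 |

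With opt-in of 70% / 50% the signs reverse. The likelihood row stands in for a model that links a participant's own waves; the Analysis plan names observations and Trusts as levels but does not name the participant level.

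**4. What the correction can and cannot do.** Dividing each group's contribution by its own opt-in rate cancels r1 and r0 in the formula above and returns 29.0% in every row. If opt-in depends on PHQ-9 status itself, it does not. With 50% opt-in among PHQ-9 cases and 65% among others, the uncorrected figure is 23.9% and the GHQ-12-weighted figure 24.9%. With the rates reversed they are 34.7% and 33.3%. The truth is 29.0% in both.

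**The case against.** The strongest reply is that this is a condensed article. Module-specific weights, attrition weights and missing-outcome methods commonly sit in an analysis plan that is not shown, and the planned comparison of short-only with short-plus-long completers is the natural first step towards a correction. That stands against any claim that the team has ruled out such methods. It does not fully answer the point, because the article does state a weighting method, names its variables, and lists the ability to weight appropriately among the study's strengths. The method as named cannot address opt-in related to distress.

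Four stronger readings are tempting, and the documents do not support them.

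- **That prevalence and change are certainly distorted.** Nothing in the protocol shows how opt-in relates to mental health. If it is equal, or explained by age, sex, ethnicity and role, there is no bias from this source. The illustration gives raking no credit for absorbing any of it.
- **That the study will report a false change of 1.8 to 3.5 points.** That needs a raw contrast between waves. The stated longitudinal analysis is a set of random-intercept models, which in the simulation cut the false change from 0.10 to 0.06 SD. The illustration also treats 6-month response as unselected; loss to follow-up could enlarge or offset the difference.
- **That the artefact is many standard errors wide.** A simple-random-sample error for one wave ignores weighting, clustering by Trust and the second wave's variance, and the protocol gives no number of respondents.
- **That imputation of outcomes is excluded.** The restriction on imputation concerns missing demographic data only.

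**Conclusion.** The point holds in conditional form. The change of module between baseline and 6 months is plain in the text, and the stated weights leave opt-in related to distress uncorrected. If opt-in depends on mental health beyond the raking variables, baseline prevalence of GAD-7, PHQ-9, AUDIT, PCL-6 and MIES outcomes will be biased, and part of any difference from 6 months will reflect who was measured. The planned models lessen this without removing it unless GHQ-12 enters them.

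Size and direction are unknown. The range of about 1.8 to 3.5 points either way for PHQ-9 rests on assumed opt-in differences of 10 to 20 points by GHQ-12 caseness and on assumed PHQ-9 caseness of 50% and 8%. GHQ-12 prevalence and trajectory are not touched by the module change. The matter should be corrected before the five outcomes are reported as prevalence or as change; it does not undermine the cohort as a whole.

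**What to change.** 1. For every outcome taken from the baseline long survey, multiply the raking weight by the inverse of the estimated probability of completing that survey, modelled on short-survey variables including baseline GHQ-12 (others available are perceived support, access to protective equipment and role).
2. Build the 6-month and 12-month weights in the same way, from baseline variables.
3. Report change in the five measures either among people measured at both waves, with these weights, or from the mixed model with baseline GHQ-12 included. The unweighted paired comparison is not enough: it left 0.03 SD of false change in the simulation.
4. Add a sensitivity analysis in which opt-in depends directly on the outcome, since GHQ-12 weighting leaves bias in that case.
5. State beside the baseline figures that these five measures came from an optional module, and show the planned comparison of short-only and long completers, including GHQ-12 caseness in each.

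The cost is some extra weighting models on data already collected and slightly wider intervals. No change to the surveys is needed.

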#### Diagnostic interview study

Participants will be up to 350 HCWs who have completed the baseline NHS CHECK survey.

Up to 250 participants will be purposively sampled according to their responses to the General Health Questionnaire (GHQ) in the short survey module;^13^ half will meet caseness and half will not meet caseness. These participants will be administered the Clinical Interview Schedule-Revised (CIS-R).^14^ The number of CIS-R interviews (n=250) has been chosen balancing precision and cost. Based on a simulation study, we anticipate that 250 interviews will allow estimation of CIS-R prevalence of common mental disorders to within ±6%.

Up to 100 HCWs will be sampled according to their responses to the 6-item PTSD Checklist civilian version (PCL-6)^15^ in the long survey module; half will meet caseness and half will not meet caseness. These participants will be administered the Clinician-administered PTSD Scale (CAPS-5).^16^ This sample size was calculated as the necessary number to achieve a valid estimation of PTSD prevalence.

Sampling for the CIS-R and CAPS-5 groups will be stratified to ensure representation from each of the 18 participating sites in the NHS CHECK Study, as well as to ensure ethnic, sex and age breakdown that resembles respondents of the baseline survey.

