## Ethical considerations

### Longitudinal cohort study

Once consented into the study, an automatically assigned ID number will be used for each participant, allowing survey data to be held pseudonymously. All study staff will adhere to relevant data protection regulations, and will maintain confidentiality at all times. No information that could identify any individual participant will be used in reports or publications, or passed on to the Trusts.

Participants will be able to stop the survey at any point, and can skip questions wherever desired. The only required questions are email address and main employing Trust. Signposting information will be provided for any participants who experience distress in answering survey questions (eg, links to websites for NHS front-line staff, Mind, Samaritans and the WHO resources for dealing with psychosocial considerations during the pandemic).

There might be some indirect benefits to the participant when taking part. People often value the opportunity to share their opinions, experiences and feelings, and several free-text options throughout the surveys offer the chance to do this.

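### Baseline outcomes collected only in the optional longer survey get no stated correction for opting in, and raking on demographics cannot remove selection related to distress

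*Protocol article*

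**What the plan says.** Protocol article, Measures, Longitudinal cohort study, Baseline. GHQ-12 is in the short survey: "The prevalence of probable common mental disorders will be assessed using the 12-item GHQ-12". The longer survey is voluntary ("There will be the option for participants to complete an additional longer survey (10–15 min"). It carries the other named instruments: "In addition, the following validated measures will be used in the longer survey: the 7-item Generalised Anxiety Disorder (GAD-7) Scale", followed by PHQ-9, AUDIT, PCL-6, BAT and others. The suicidality items are also placed there.

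Analysis plan, Longitudinal cohort study. The weighting is described as: "Response weights will be calculated for each Trust, generated using a raking algorithm based on age, sex, ethnicity and role". Margins come from Human Resources data, and missing demographics are multiply imputed for weighting only. Then: "We will summarise the weighted prevalence of the primary and secondary outcomes, stratified by sociodemographic and occupational factors". No distinction is made between short-survey and long-survey outcomes. Short-only participants will be compared with those who complete both modules. No weight, imputation or sensitivity analysis is tied to the result.

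Ethical considerations, Longitudinal cohort study: "The only required questions are email address and main employing Trust".

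Study population and sample, Diagnostic interview study. The CAPS-5 frame rests on a long-survey measure: "Up to 100 HCWs will be sampled according to their responses to the 6-item PTSD Checklist civilian version". The analysis plan for that component would project prevalence, if possible, with weights from sex, age and ethnicity.

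**The concern.** Baseline has two stages of self-selection: answering the survey at all, then opting into the longer module. The stated adjustment names four demographic and occupational variables. It contains nothing about mental health, although GHQ-12 is collected in the short survey and is likely to predict the long-survey outcomes strongly. If distressed staff are less willing, or keener, to go on to another 10 to 15 minutes of questions, the weighted prevalence of probable depression, anxiety, PTSD, hazardous drinking, burn-out and suicidality is shifted, and a larger cohort does not reduce the shift.

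Two uses of the data would inherit the problem.

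- **Change over time.** The 6-month section lists GAD-7, PHQ-9, AUDIT, PCL-6 and the suicidality items ahead of its paragraph on the long survey, which suggests that they move to the short module. On that reading, baseline describes long-survey volunteers and 6 months describes all responders, so a change of module could look like a change over time. BAT stays in the long module.
- **CAPS-5.** Any projection from the CAPS-5 interviews starts from long-survey completers.

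**Working it through.** The article gives no long-survey uptake and no weighted prevalence, so there is no figure of its own to reproduce. The inputs below are assumptions, chosen to show size.

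**1. Demographic margins, if all responders are raked.** Assume two role groups of equal size in the Trust (s = 0.5 each), with long-survey completion c of 50% and 75%. The weighted share among completers is s·c / Σ(s·c):

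0.5×0.50 / (0.5×0.50 + 0.5×0.75) = 0.25 / 0.625 = 40%, against a target of 50%.

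Effect on prevalence: assume two equal groups with true prevalence 35% and 20% (27.5% overall) and mean completion 60%. The all-responder weights give:

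| Completion gap between groups | Weighted prevalence | Bias (points) |
|---|---|---|
| 0 | 27.5% | 0 |
| 5 points | 27.2% | −0.3 |
| 10 points | 26.9% | −0.6 |
| 20 points | 26.2% | −1.3 |
| 30 points | 25.6% | −1.9 |

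For example, at 30 points: (0.35×0.45 + 0.20×0.75) / (0.45 + 0.75) = 0.3075 / 1.20 = 25.6%. Re-raking among completers returns 27.5% in every row.

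**2. Opt-in that depends on GHQ caseness.** Assume GHQ caseness g of 40% to 60%, and a PHQ-9 case rate of 45% in GHQ cases and 7% in non-cases. With completion c1 in cases and c0 in non-cases, the share of GHQ cases among completers is g′ = g·c1 / (g·c1 + (1−g)·c0), and the bias in PHQ-9 prevalence is (g′ − g) × (0.45 − 0.07).

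| g | True PHQ-9 prevalence | g′ at 60% v 70% | Bias (points) | g′ at 50% v 75% | Bias (points) |
|---|---|---|---|---|---|
| 40% | 22.2% | 36.4% | −1.4 | 30.8% | −3.5 |
| 50% | 26.0% | 46.2% | −1.5 | 40.0% | −3.8 |
| 60% | 29.8% | 56.3% | −1.4 | 50.0% | −3.8 |

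With the completion rates swapped, so that cases are keener, the bias is +1.4 to +1.5 and +3.5 to +3.8. With equal completion, g′ = g and the bias is zero.

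**3. Does the choice of raked set matter for this part?** Take the two groups in step 1, but let completion depend on outcome caseness, averaging the two rates to 60%:

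| Completion, cases minus non-cases | Raked on all responders | Re-raked on completers | Truth |
|---|---|---|---|
| −20 points | 21.3% | 21.5% | 27.5% |
| −10 points | 24.3% | 24.4% | 27.5% |
| +10 points | 31.0% | 30.8% | 27.5% |
| +20 points | 34.7% | 34.5% | 27.5% |

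Re-raking on demographics changes the answer by 0.1 to 0.2 points and leaves a bias of about −6 to +7 at the extremes.

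**4. Against sampling error.** The 18 Trust counts in the article sum to 151,153. Assume 5% response (the article's floor for keeping a Trust) and 60% long-survey uptake: 151,153 × 0.05 × 0.60 ≈ 4,535 completers. At 26% prevalence the 95% half-width is 1.96 × √(0.26×0.74/4,535) ≈ 1.3 points, or 1.3 × √2 ≈ 1.8 with an assumed design effect of 2. The 3.5 to 3.8 point bias exceeds both. A higher response narrows the interval but not the bias.

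**5. What a GHQ-based weight does.** In step 2 with g = 50% and completion 50% v 75%, completers make up 0.25 (cases) and 0.375 (non-cases) of responders. Dividing by the completion rates gives 0.50 and 0.50, so the 26.0% is recovered. In step 3, where opting in follows the outcome itself, a GHQ-based weight would correct only the part that GHQ-12 and the other short-survey items predict.

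**The case against.** A reader might infer that one set of weights, raked over everyone who responds, is reused for the long-survey outcomes, and that those figures therefore do not represent the Trust. The article does not support that. It calls them response weights and imputes demographics so that people who skipped them can be weighted, which points towards all responders. But it neither names the raked set nor says that the weights are reused. If completers are raked for long-survey outcomes, step 1 falls away. Nor is bias certain: it is zero when opting in is unrelated to demographics and distress, and no uptake figures are given.

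It is also fair to say that this is a condensed article, that module-specific weights may appear in a fuller plan, and that the short-versus-long comparison shows the authors recognise the selection. The definition of the raked set can reasonably be left to that plan. What does not fall away is that the article specifies its adjustment in some detail (variables, margin source, imputation rule), mentions the short/long split beside it, and attaches no correction. As stated, the method cannot deal with distress-related opt-in, whichever set is raked.

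The reach is limited too. GHQ-12 is in the short survey, so its prevalence does not depend on the opt-in. The true prevalence of disorder is assigned to the diagnostic interviews. For CAPS-5, the article makes projection conditional and allows sensitivity analyses for missingness, though the weighting variables it names there are again only demographic.

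**Conclusion.** The point holds in a conditional form. Weighted baseline prevalence of PHQ-9, GAD-7, AUDIT, PCL-6, BAT and suicidality may be biased in either direction, because the stated adjustment covers demographics and role but not opt-in related to distress. On the step 2 assumptions the size for PHQ-9 is about 1.5 points for a moderate difference in completion and 3.5 to 3.8 points for a large one. Demographic imbalance adds to this only if all responders are raked and long-survey completion differs across the raking variables. The completion rates and case rates are assumptions, so the figures show what is possible, not what will occur.

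**What to change.** State which respondents are raked for each outcome. For baseline long-survey outcomes:

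1. Model the probability of having a valid score on GHQ-12 score, age, sex, ethnicity, role, Trust and other short-survey items such as the COVID-19 and support questions. Allow for responders who stopped before GHQ-12, since participants may stop at any point.
2. Multiply the response weight by the inverse of that probability.
3. Re-rake to the Trust margins among those with a valid score.
4. Use this weight when projecting CAPS-5 results beyond long-survey completers.

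Report the demographic-only weighted estimate alongside, so that the effect of the second stage is visible. The planned short-versus-long comparison can guide the choice of variables.

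The cost is one extra model for the long module, on data already collected, with slightly more variable weights and wider intervals. The correction is only as good as the short-survey items: selection that they do not capture remains and should be stated as a limitation.
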